## Participants

Participants will be recruited from March to September 2013 by public advertisement in the Porto metropolitan Area from be from Porto University Faculties, by journal, media and through the academic organization information. In the advertisement a simple explanation will be provided about the study. Eligibility criteria will be: target age from 18 to 35 years old, have controlled asthma (which answered positively to the question have you ever been diagnosed with asthma by a medical physician? and controlled assessed by Asthma Control Questionnaire e o CARAT- **Attachment 7**), obese and non-obese and healthy participants for control group.

Groups will be stratified by having asthma and by their IMC in 4 groups: Asthmatic and obese; asthmatic non-obese; obese and non-asthmatic and non-obese. Patients will be considered as obese if they have  $BMI \geq 30 \text{ kg/m}^2$

Exclusion criteria will be: smoking in the past 6 months, abnormal electrocardiogram screening, pregnancy, diabetes mellitus, cardiac arrhythmia, angina, congestive heart failure, renal or hepatic failure and systemic disease, mal-absorption disease history, intestinal inflammatory disease, unable to adhere to full intervention or complete follow-up, unable to perform lung function testing and impaired mental status that makes difficult to follow or understand the instructions. Non-obese healthy controls need to have: no respiratory symptoms, had never a doctor's diagnosis asthma, normal lung function and have to be steroid-naïve.

## Procedures

After recruitment an interview will be performed to verify if patient verifies the inclusion criteria. This interview will assess weight and height, previous history of asthma and its control, presence of co-morbidities and availability to the study intervention and follow-up. If included a baseline assessment will be performed in the same day.

Baseline assessment will consist in obtaining information about: demographic characteristics, assessment of co-morbidities, anthropometric measure, blood pressure, rest heart rate, pupilometry, nutritional assessment, lung function measured by spirometry and bronchodilation, atopy assessed by skin prick test, basal physical activity assessment through a questionnaire, patients will also use an accelerometer for 7 days to evaluate their daily physical activity.

### Randomization and blinding

Patients will be informed of the procedure but they will be blinded to which is the intervention (high fat or low fat meal). Stratified blocked randomization will be performed accordingly to being asthmatic or obese. This methodology was chosen despite acute changes are the aim, to exclude and evaluate the intervention order in the studied outcomes. Equal number of participants will be allocated to each group.

Allocation concealment will be prevailed as investigator will only know the intervention order for that participant at the moment the meal is provided. Exercise challenge and outcome assessment, namely urine, blood sample collection, exhaled breath condensate and lung function will only be performed by another investigator blinded to the meal order.

### Intervention:

Meal challenge will be of high fat and low fat meal. Both meals composition will be controlled and built by a nutritionist team. All food left in the plate will be evaluated and registered to understand the caloric ingestion of each participant. No restrictions will be imposed previously neither diet control, as acute changes are the main outcome of this study and a daily diet diary will be provided. Only patients with controlled asthma can start the intervention, in the day of the first challenge they will return the accelerometer.

After the meal challenge, participants will not be allowed to eat or drink, in exception to water, and cannot perform any physical exercise. Then they will be taken to an exercise challenge laboratory, at Sports Faculty of Porto University, there 3 hours after the meal challenge blood, urine sample and exhaled breath condensate will be collected, heart rate at rest registered, skin test reactivity with histamine and spirometry performed. Exercise challenge, after the measurements 1 or 2 (figure 1) will be done. During the exercise heart rate response, exhaled VO2, CO2 and symptoms will be systematically registered. A physician and a cardiopulmonary technician will follow the challenge. Immediately after, a spirometry will be done and then at 5, 10 and 15 min after stopping the run, induced bronchoconstriction, pupillometry will be also measured and skin test with histamine and new blood and urine samples will be taken. If a fall in FEV1 over 10% occurs, bronchodilation will be done and patient treated. The exercise challenge will take at minimum 8 min, and patient will be asked to perform maximum effort, as the aim is to maintain for 4 min the heart rate at 95% of the target heart rate (220-rest heart rate).

Blood, exhaled air condensate, urine and saliva obtained before and after the exercise challenge will be used to analyze: metabolomic markers, immune function and inflammatory measures (in ex. leukocytes, lymphocytes, neutrophils, lymphocytes subpopulations and cytokine reduction, like IL-1, IL-6 and IgA in the saliva), stress mediators/hormones (ex. blood cortisol, growth hormone and epinephrine), endocrinological markers (ex. insulin, resistin, adiponectin, PAI-1, leptin) and fatty acids level (ex. monounsaturated, polyunsaturated and saturated fatty acids). Skin test sensitivity will be evaluate by histamine reactivity.

Patient will then go through a wash-out period of a week to avoid carry-over effect, as previously published intense acute exercise inducts changes in immune parameter that are maintained elevated for hours. It was also suggested an association between creatine kinase and IL-6 levels and the first can stay increased after exercise for almost 4 days after acute exercise challenge and by that the IL-6 level could be increase if shorter period of wash-out would be selected [14, 25].

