#### **4.1.4. Effect of an high fat meal on neuro-immune-endocrine response to an acute exercise challenge (IV)**

This is a randomized cross-over trial, with a wash out period of 7 days, single-blinded, placebo controlled. Study design is specified in figure 1. Participants will be recruited from advertisement and four different groups will be compared: obese-asthmatic; asthmatic non-obese; obese without asthma and non-asthmatic and non-obese. Stratification will be done accordingly to having asthma and  $BMI \geq 30 \text{ kg/m}^2$ . All patients will be allocated to a meal challenge in which a high fat meal will be followed by a low fat meal or vice-versa, meal challenge order will be randomized and participants blinded to the intervention. Three hours after it will be followed by an exercise challenge, which is aimed to induce acute immune changes. The main outcome will be exercise-immune function (immune function markers) changes after a diet challenge. As secondary outcomes stress/inflammatory markers, endocrine mediators, as well as blood fatty acids will be measured. Lung function,  $VO_2$  and airway inflammation will be assessed by exhaled breath condensate inflammatory markers and eNO. Any adverse events of the challenge will be registered, namely respiratory infections, gastro-intestinal symptoms and muscular ache.

[figure not shown]

**Figure1.** Randomized cross-over study trial, single-blinded to meal intervention. Measures (1.1; 1.2;2.1;2.2) immediately before and after exercise challenge include: Immune-endocrine-metabolomic response (blood, urine and saliva samples); Pupilometry; Lung-function and VO2 consumption; skin prick histamine reactivity

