#### **4.2.9. Exercise challenge (IV)**

Protocol will be performed accordingly as previously published and aimed to access physical fitness, exercise induced bronchoconstriction [59, 60].

Contra-indications to perform exercise testing will be: moderate to severe airflow limitation (predicted FEV1<60% or <1,5L), heart attack or stroke in the last 3 months, uncontrolled hypertension (systolic BP>200 or diastolic BP>100), malignant arrhythmias, know aortic aneurysm, orthopedic limitations to exercise, inability to perform acceptable-quality spirometry, pregnancy, nursing mothers, current use of cholinesterase inhibitor medication (myasthenia gravis).

The challenge will be performed in controlled conditions, ambient temperature between 20-25°C, with low relative humidity (less or equal to 50%). Heart rate will be monitored during all test by a reliable measurement (three lead electrocardiographic configuration or pulse oximeter), nasal clips will be used during the test and blood pressure will be taken before the challenge.

Exercise challenge will be done in a treadmill with starting with a slope of 5.3% and consists: in a 2 min warm up until the heart rate achieved 70-80% of the estimated HR peak, calculated as  $(220 - \text{age [years]})$ , (ventilation can also be used to monitor and should reach 40-60% of the predicted maximum voluntary ventilation, estimated by  $\text{FEV}_1 \times 35$ ). The speed will then be adjusted during the first 4 minutes to achieve a workload corresponding to the maximum speed subjects will be able to sustain for the last 4 min, about 95% of the estimated HR. This test usually requires 6 to 8 min, but longer period of time will be needed and will be adjusted to an individual basis and the patient physical condition. At the end of the test  $\text{VO}_2$ , VE, RER, and HR will be measured as well as lung function, namely maximal forced expiratory flow volume loops at 1, 3, 5, 10, 15 and 20 minutes after the challenge. In all patients bronchodilation with salbutamol will be performed after 15 min.

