Exercise testing (IV), namely maximal symptom-limited exercise testing is a relatively safe procedure, especially in otherwise healthy individuals. Fatality risk is related to medical complications to the underlying disease and the rate of death per patients during exercise testing is 2 to 5 per 100.000[75]. Strict contra-indications will be followed. A licensed physician and an cardio-respiratory technician will observe the participant during exercise and the recovery period and watch for undue stress (e.g., severe wheezing, chest pain, lack of coordination) or adverse signs (e.g., ECG abnormalities, falling blood pressure, decrease in O2 saturation), if it occurs the test will be immediately stopped and any adverse event treated. A resuscitation cart will be immediately available. The population tested in this study will be young and otherwise healthy without know disease, only chronic co-morbidity will be asthma and obesity. Exercise induced bronchoconstriction is assessed by exercise challenge and it is a recommended and widely used method to evaluate asthma patients. Furthermore these population will be under controlled asthma. If any adverse event occurs, namely bronchoconstriction it will be immediately reversed with bronchodilation.

Exercise intervention in the elderly population (III), was already submitted and accepted by the ethical commission (**Attachment 6**). Moderate exercise program will be performed and adapted to each elderly participant, co-morbidities and difficulties and physical condition and anaerobic resistance for exercise strength will be evaluated previously to the training by resistance maximum. Exercise will then be adapted to each individual condition and progressively increased at each participant rhythm. The exercise will be guided by sports professors trained in exercise teaching and monitoring. Potential adverse conditions can occur, namely muscle and body ache which will be self-limited and prevented by this progressive adaptation to exercise. All elderly will have an individual insurance if any adverse event occurs, namely falls during training or any unavoidable accident.

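### Study IV: section 4.1.4 sets the exercise target from 220 minus resting heart rate, while section 4.2.9 uses 220 minus age for the same challenge

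*Protocol*

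**What the plan says.** Two parts of the Protocol set the intensity of the Study IV exercise challenge.

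- **Section 4.1.4, Intervention.** The instruction on duration and effort is that "The exercise challenge will take at minimum 8 min, and patient will be asked to perform maximum effort". The reason given is that "the aim is to maintain for 4 min the heart rate at 95% of the target heart rate (220-rest heart rate". The reference value is therefore 220 minus the resting heart rate.
- **Section 4.2.9, Exercise challenge (IV).** The test consists "in a 2 min warm up until the heart rate achieved 70-80% of the estimated HR peak, calculated as" 220 minus age in years. Speed is then adjusted to reach "the maximum speed subjects will be able to sustain for the last 4 min, about 95% of the estimated HR". The only estimated heart rate defined in that section is the peak, 220 minus age.

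Three other statements bear on the point. Section 4.1.4 (Participants) sets a "target age from 18 to 35 years old". Section 5 (Safety) describes the Study IV test in the terms "namely maximal symptom-limited exercise testing is a relatively safe procedure". The opening of section 4.1.4 says that the meal is "followed by an exercise challenge, which is aimed to induce acute immune changes".

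**The concern.** Both sections describe the same 4-minute plateau of the same treadmill test, yet they compute its target from different quantities, and nothing in the protocol reconciles them. Resting heart rate in a young adult is normally well above age in years, so subtracting it from 220 gives a much lower figure than subtracting age. The 4.1.4 target then cannot be squared with the maximum effort requested in its own sentence, or with the maximal test described in section 5.

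What is at stake is the dose of the exercise stimulus. The main outcome of Study IV is the change in immune markers with exercise after a diet challenge, so the exercise has to be hard enough to produce that change. Staff who worked from the 4.1.4 formula would stop well short of it. The dose would also depend on a baseline characteristic: people with higher resting rates would receive lower targets, in a study that compares four groups defined by asthma and obesity.

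Section 4.1.4 further has resting heart rate recorded both at baseline and on each challenge day, 3 hours after the meal, without saying which value enters the formula. If the same-day value were used, one person's target could differ between the two periods. Age raises no such question.

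**Working it through.** **Inputs**

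- Age: 18 to 35 years (section 4.1.4, Participants).
- Target A: 0.95 × (220 − resting rate) (section 4.1.4, Intervention).
- Target B: 0.95 × (220 − age) (section 4.2.9).
- Warm-up: 0.70 to 0.80 × (220 − age) (section 4.2.9).
- Resting rate: not given in the protocol. Assumed to be 60 to 80 bpm, with 50 to 90 bpm as a wider range.

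The protocol states formulas but no target in bpm, so there is no printed figure to reproduce.

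**Target B (section 4.2.9)**

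- Age 18: 0.95 × 202 = 191.9 bpm.
- Age 25: 0.95 × 195 = 185.25 bpm.
- Age 35: 0.95 × 185 = 175.75 bpm.

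**Target A (section 4.1.4)**

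- Rest 50: 0.95 × 170 = 161.5 bpm.
- Rest 60: 0.95 × 160 = 152.0 bpm.
- Rest 70: 0.95 × 150 = 142.5 bpm.
- Rest 80: 0.95 × 140 = 133.0 bpm.
- Rest 90: 0.95 × 130 = 123.5 bpm.

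**Difference**

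B − A = 0.95 × (220 − age) − 0.95 × (220 − rest) = 0.95 × (rest − age). This is zero only if the resting rate equals the age, which here means 18 to 35 bpm. Above that, A is always the lower target.

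| Assumed resting rate | Smallest gap (age 35, lowest rate) | Largest gap (age 18, highest rate) | Target A as % of 220 − age |
|---|---|---|---|
| 60–80 bpm | 0.95 × (60 − 35) = 23.75 bpm | 0.95 × (80 − 18) = 58.9 bpm | 133/202 = 65.8% to 152/185 = 82.2% |
| 50–90 bpm | 0.95 × (50 − 35) = 14.25 bpm | 0.95 × (90 − 18) = 68.4 bpm | 123.5/202 = 61.1% to 161.5/185 = 87.3% |

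**Comparison with the protocol's own warm-up**

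At age 25 the section 4.2.9 warm-up runs from 0.70 × 195 = 136.5 to 0.80 × 195 = 156.0 bpm. Target A at resting rates of 60 to 80 bpm is 133 to 152 bpm. Read literally, the main effort in section 4.1.4 sits at about the level that section 4.2.9 reaches in its 2-minute warm-up, against a section 4.2.9 plateau of 185.25 bpm.

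**The case against.** The best defence is that the document already shows what was meant. Section 4.2.9 is the dedicated procedure, with slope, warm-up, speed adjustment and monitoring, and it defines the peak correctly. The 4.1.4 formula is a short parenthesis in an account of the visit. Maximum effort is requested in the same sentence, and section 4.2.9 asks for the highest speed the participant can sustain over the last 4 minutes. Staff who followed section 4.2.9 would be at or near the 4.1.4 figure by the end of the warm-up and would notice the clash. Under-dosing therefore requires someone to overlook all of this.

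Three narrower points also have merit:

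- Section 5 describes a maximal test; it does not instruct one.
- Section 4.2.9 says estimated heart rate at the 95% step, so reading this as 220 minus age is an inference, though no other estimated heart rate is defined there.
- The gaps in bpm rest on assumed resting rates, and the ends of each range pair extreme ages with extreme rates.

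All of this limits the likely harm, and the size of the gap is illustrative. It does not make the 4.1.4 formula right. That formula stands in the section that sets out the intervention, and the direction of the error holds for any resting rate above the participant's age.

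**Conclusion.** The concern holds. Section 4.1.4 gives a wrong reference value for the 4-minute plateau, and it conflicts with section 4.2.9. At ages 18 to 35 the intended target is 176 to 192 bpm. The formula as written gives 133 to 152 bpm at assumed resting rates of 60 to 80 bpm, a shortfall of 24 to 59 bpm (14 to 68 bpm if resting rates run from 50 to 90). The direction does not depend on these assumptions; the size does.

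This should be corrected because it fixes the intensity of the stimulus behind the main outcome. Its reach is limited. The meal comparison is within-subject and stays fair provided the same target applies in both periods. Power and alpha are unaffected, and no harm to participants follows from a target that is too low.

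**What to change.** In the Intervention part of section 4.1.4, replace 220 minus resting heart rate with 220 minus age, so that the target matches section 4.2.9. State that each participant has the same target in both periods.

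The cost is a one-phrase correction and one added sentence. Design, sample size and visits do not change. The protocol is dated 10 December 2012 and recruitment is planned from March 2013, so the change can be made before anyone is enrolled.

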#### **4.1.5. Physical activity reduction effect on immune response (V)**

This is a randomized controlled trial where participants, after a run-in period and eligibility evaluation, will be randomized to an intervention consisting in a reduction of physical activity by 50% or maintaining habitual physical activity for two weeks. Participants will be recruited from the same population as the meal-exercise challenge study and stratification will be done accordingly to having asthma and  $BMI \geq 30 \text{ kg/m}^2$  in order for both characteristics could be balanced between groups.

Participants will be at baseline characterized for their nutritional status, dietary habits and physical activity through questionnaire and basal assessment of all sports activity practiced during a week. Also generic quality of life questionnaire will be applied. A pedometer and accelerometer will be used to monitor physical activity. After this run-in period, if they have an adequate physical activity they will be allocated randomly to one of the interventions. Calculation of physical activity reduction will be performed individually, and a daily steps target will be demanded for each group. Both groups will use a pedometer during 3 weeks, except during the night or at circumstances that the device might be damaged (bath). They will be able to monitor if they achieved or exceeded the target number of steps for that day. Keeping the same regular diet without any new changes will be requested and new recall dietary assessment will be also performed in the end of the study. Immune function mediators will be the primary outcome to be assessed before and after the intervention period in both groups. As secondary outcomes endocrine and metabolomic evaluation will be performed.

#### **Participants**

Participants will be recruited from March to September 2013 by public advertisement in the Porto metropolitan Area from Porto University Faculties, by journal, media and through the academic organization information. Same participants recruited for the meal-exercise challenge trial will be invited to participate in the physical activity reduction. Eligibility criteria will be 18 to 35 years old, able to perform exercise. In this study a run-in period will be demanded to evaluate inclusion criteria. In all participants daily-life physical activity will be evaluated and use a pedometer for a 7 day period to evaluate the mean number of steps/day. Only those with more than 3500 steps per day will be included for randomization. Inclusion criteria will be: target age 18 to 35 years, healthy, nonsmokers, revealed no physical abnormalities and were physically active (performed  $>3500$  steps/day). Groups will be balanced in the characteristics: having asthma and if they are obese ( $BMI \geq 30 \text{ kg/m}^2$ ) or non-obese.

Exclusion criteria will be: smoking in the past 6 months, pregnancy, diabetes mellitus, cardiac arrhythmia, angina, congestive heart failure, renal or hepatic failure and systemic disease, unable to adhere to full intervention or complete follow-up, impaired mental status that makes difficult to follow or understand the instructions.

#### **Procedures**

After recruitment an interview will be performed to verify if patient meets the inclusion criteria for study inclusion. This interview will assess weight and height, previous history of asthma and its control, presence of co-morbidities and availability to the study intervention and follow-up. If eligible, a run-in period will be performed that include: baseline assessment and a 7 week daily assessment of physical activity by a pedometer and accelerometer.

Baseline assessment will consist in: nutritional assessment, quality of life questionnaire (**Attachment 2**), asthma control questionnaire in asthmatic patients (**Attachment 7**), blood pressure, rest heart rate measurements, pupillometry, lung function measured by spirometry and bronchodilation, atopy assessed by skin prick tests, basal physical activity evaluated by Baecke (**Attachment 8**) and International Physical Activity questionnaire(**Attachment 9**). Physical activity will be also accessed by accelerometer and pedometer; only subjects that perform more than 3500 steps/day will be included. All other participants that are not eligible will receive dietary and physical activity written recommendations.

#### Randomization

Stratified blocked randomization will be performed accordingly to being asthmatic or obese. This methodology was chosen in order for both groups to be balanced for intervention comparison. Neither the participants or investigator team will be blind to the intervention procedure as there is a need to monitor number of steps/day to be compliant with the prescribed physical activity diary (keeping the same mean steps or reducing by 50% the number of steps/day). Equal number of participants will be allocated to each group.

Allocation concealment will be prevailed as investigator and participant will only know the intervention that they will be submitted at the second visit.

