### **Methods:**

Study design: An observational study with validation methodology will be applied to evaluate respiratory infections; in prospective cohort study of 12 weeks a group of athletes under high competition levels, respiratory infections and potential risk factors accordingly to literature will be evaluated; an prospective case-control with a moderate- exercise program intervention will compare the impact in respiratory infections in elderly under exercise training or not; a randomized, placebo controlled cross-over trial will evaluate the impact of a high fat/high energy meal challenge in an acute exercise challenge; randomized clinical trial will be used to ascertain the impact of physical activity reduction in the immune function

Selection of participants: For questionnaire validation will be selected participants with respiratory infections; athletes will be selected from a high elite pre-competition level team; elderly will be selected from general population, namely from senior universities and nursing homes; asthma and obese participants will be selected from an university population sample

Sample Size: 281 patients will be chosen as target for evaluation in respiratory tract infections validation; 40 patients will be evaluated in total in swimmers illness-prone study trial; 40 participants will be selected to evaluate exercise program in the elderly; 30 participants, with a

equal number of obese, asthma, obese and asthma and a control will be allocated to the meal interventions (60 participants in total) and a target of 60 participants will be randomized to the physical inactivity intervention.

Measurements: Upper respiratory tract infections number, severity and quality of life impact, immune system markers, complete blood cell count, pro-inflammatory and anti-inflammatory mediators, namely cytokines, and metabolomic.

Main Outcomes: Respiratory Infection Risk in Susceptible Population, Immune markers parameter related with acute exercise and physical inactivity interventions (balance between pro-inflammatory and anti-inflammatory cytokines).

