### 4.3. Statistical analysis (I-V)

All statistic analyses will performed using the SPSS 20.0 software (Chicago, Ill) and Excel, Microsoft Office, for data assembly and graphical analysis. Normality of data distribution will be assessed by the Kolmogorov-Smirnov test, histogram and QQ plot distribution. Results will be expressed as median and inter-quartile range or mean and standard deviation and in discrete variables as count and percentage. If a normal distribution is described t-test-student would then be used in continuous variables. For non-normal data, non-parametric tests, namely Mann-Whitney will be used, to compare groups. Measures with discrete distributions are expressed as counts (%) and analyzed with Pearson-Chi Square or Fisher exact test. The minimum threshold for statistical significance will be  $p \leq 0.05$ . In data with skewed distributions, logarithmic transformation will be done and if appropriate (normal distribution is achieved) comparisons will be made with this change.

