### **4.3.4. Reducing physical activity (V)**

The analysis was conducted using the “intention-to-treat” (ITT) approach, including all randomized subjects which took at least one dose of the study preparation/or intervention and who had at least one post-baseline efficacy variable measurement. Changes between baseline and after intervention period was analyzed with paired t-tests. The absence of studies evaluating the immunological outcomes precluded the power analysis.

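### Study V randomises within asthma and obesity strata, but its stated tests use neither factor, so an unadjusted between-arm standard error would be too large to the extent that the strata predict the outcome

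*Protocol*

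**What the plan says.** The Randomization part of section 4.1.5 states: "Stratified blocked randomization will be performed accordingly to being asthmatic or obese". The reason follows: "This methodology was chosen in order for both groups to be balanced for intervention comparison". The opening of 4.1.5 gives the same aim for asthma and BMI >=30, "in order for both characteristics could be balanced between groups". Allocation is 1:1 ("Equal number of participants will be allocated to each group"), and the Summary gives the size as "a target of 60 participants will be randomized to the physical inactivity intervention". On the outcome, 4.1.5 says: "Immune function mediators will be the primary outcome to be assessed before and after the intervention period in both groups".

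The analysis is in section 4.3.4. Apart from defining the analysis set and explaining why there is no power calculation, it says only: "Changes between baseline and after intervention period was analyzed with paired t-tests". It names no asthma or obesity term and no test of one arm against the other.

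The general rules in section 4.3 supply the only two-group tests that could apply: "If a normal distribution is described t-test-student would then be used in continuous variables", with Mann-Whitney for non-normal data. The regression models with named covariates in section 4.3.2 are for Studies II and III.

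**The concern.** Blocked allocation within strata forces the arms to be alike in asthma and obesity. Variation between strata then no longer contributes to chance differences between the arms. A two-sample test that ignores the strata still counts that variation in its error term, so it reports more uncertainty than the design leaves.

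Section 1 of the protocol links asthma and obesity to a chronic inflammatory profile, and the primary outcome is a set of immune mediators. It is therefore reasonable to expect the strata to be related to at least the level of the outcome. At stake are interval width and power for the effect of step reduction, in a small trial for which the protocol gives no power, effect size or standard deviation.

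**Working it through.** **Inputs from the protocol.** Two binary stratification factors (asthma; BMI >=30), so 2 x 2 = 4 strata. A target of 60 people, read as the total, and 1:1 allocation, so 30 per arm. Significance threshold 0.05.

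**Assumptions.** The test is two-sided (sidedness is not stated). Strata are of similar size (16, 16, 14 and 14). R2, the share of within-arm variance of the analysed outcome explained by the four strata, ranges from 0 to 0.30. The protocol gives nothing from which to fix it.

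**No figure to reproduce.** The protocol states no power for Study V. For scale, the standardised difference detectable with 80% power at 30 per arm is (1.960 + 0.842) x sqrt(2/30) = 0.72.

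**Formula.** Take a total within-arm SD of 1.

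- Standard error reported by the unadjusted t-test: about sqrt(2/30) = 0.258, whatever R2 is.
- True standard error of the difference when arms are balanced within strata: sqrt(2/30) x sqrt(1-R2).
- Ratio of reported to true: 1/sqrt(1-R2).

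Example at R2=0.20: 0.258 x sqrt(0.80) = 0.231, and 1/sqrt(0.80) = 1.118, so the reported standard error is 11.8% too large.

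**Simulation check.** 20,000 trials per setting; two-sample t-test (58 df) against a linear model with stratum terms (60 - 5 = 55 df). Power is at a difference of 0.735 SD, which gives about 80% when R2=0.

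| R2 | Excess in reported SE | Type I error, unadjusted / adjusted | Power, unadjusted / adjusted |
|---|---|---|---|
| 0 | 0% | 4.8% / 4.8% | 80.2% / 80.0% |
| 0.05 | 2.6% | 4.3% / 4.9% | 80.6% / 81.9% |
| 0.10 | 5.4% | 3.8% / 4.9% | 81.2% / 83.8% |
| 0.20 | 11.8% | 3.0% / 5.2% | 82.1% / 87.7% |
| 0.30 | 19.5% | 2.0% / 5.2% | 83.3% / 91.3% |

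At R2=0.20 the simulated true standard error was 0.232, against 0.258 reported without adjustment and 0.230 with it.

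A separate simulation at a smaller difference, 0.5 SD, gave power without and with strata of 47% and 51% (R2=0.10), 48% and 57% (0.20), and 48% and 63% (0.30).

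These figures are for the t-test. The size of the effect for Mann-Whitney was not computed.

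**The case against.** **Section 4.3.4 contains no between-arm standard error.** A paired t-test gives a before-after standard error within an arm. A reader might infer that the between-arm intervals of Study V are known to be too wide. The documents do not support that: the point applies only if the arms are compared with the unadjusted tests of section 4.3. This objection stands, and it means the fix must first create the comparison.

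**The excess may be nil.** Section 4.3.4 analyses change from baseline, which already removes stable differences in level between strata. The chronic inflammatory profile in section 1 is a statement about level. Section 1 also suggests that responses to acute exercise may be stronger in people with chronic inflammatory disease, but that is conjecture and concerns a different stimulus. So the range must start at R2=0, where nothing is lost, and change scores probably lie toward its low end.

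**Precision is not lost.** A reader might infer that ignoring the strata throws away what stratifying bought. The true sampling error does shrink; only the reported one fails to show it. Nor is there bias or an inflated false-positive rate.

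**It does not hold for every between-arm test.** An adjusted or stratified test would not have this fault.

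**Covariates are often left to the SAP, which is not shown.** This is fair in general, and stratifying for balance does achieve balance without adjustment. But this protocol names covariates for Studies II and III. For Study V it names tests that cannot carry the stratification factors. That is a stated analysis that does not match the stated design, not merely a detail left open.

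**Conclusion.** The point holds in conditional form. Study V randomises on two factors that none of its stated tests can use. If the arms are compared by the unadjusted t-test, the reported standard error is too large by 1/sqrt(1-R2): none at R2=0, rising to about 20% at R2=0.30. The true type I error then falls below 5%, to about 2% at R2=0.30.

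The consequence is a conservative test and some forgone power, not a misleading positive result. R2 is assumed throughout, and the calculation also rests on 60 people in total, similar stratum sizes and a two-sided 5% test. The absence of any between-arm comparison in 4.3.4 is the larger gap, and both can be closed with the same amendment.

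**What to change.** In section 4.3.4, replace the paired t-tests as the basis for inference with a between-arm comparison of each immune outcome. Use a linear model of the post-intervention value on arm, baseline value, asthma (yes/no) and BMI >=30 (yes/no), and report the adjusted difference between arms with its 95% confidence interval. The log transformation that section 4.3 already foresees for skewed data can be kept. Paired before-after changes may remain as description within each arm.

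The cost is a short change of text and about three degrees of freedom: with an intercept the model has five parameters, leaving 60 - 5 = 55 df against 58 for a two-sample t-test. No new data are needed, since both factors are known before randomisation and the baseline marker is already collected. If the strata are not prognostic, the power loss is negligible: 80.0% against 80.2% in the simulation of the stratum-adjusted model.
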